### Statistical analysis

Subgroup analysis of previous medical history exposure to antibiotics, infections in pregnancy and indication for delivery will be performed on an exploratory basis. Adjustments for recall rate (diary, survey data) will be performed, we aim for a recall-rate of > 75%.

Statistics will be performed with R version 4.2 or higher. For graphs Graphpad prism version 10.1.2. will be used. Details of the statistical analysis will be fixed in a statistical analysis plan, which will be finalized by the trial statistician before inclusion of the last patient. The duration of probiotic intake will be taken into account in the final analysis. We will adjust our data for the different intervention timeframes using matched pair and multivariate regression analyses. However, the duration of pregnancy-accompanied probiotic therapies that were necessary to achieve the investigated outcome effects in the various studies performed (see Table 1.) have not yet been investigated. Consequently, in the case of observed effects of probiotic therapy on the HMO concentration, we will also determine the necessary duration of supplementation as a result of this study.

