### In- and exclusion criteria

Pregnant women of any ethnic background between 20 + 0 and 36 + 6 weeks of pregnancy who are at risk for preterm birth are included. The underlying condition (e.g. PPROM, cervical shortening, bleeding, preeclampsia, HELLP syndrome) is not decisive to inclusion. Participating patients will be included after they have been informed about the study procedures, intervention, associated responsibilities and when they have given written informed consent. Women with outpatient monitoring are also applicable for participation. Since the date of birth cannot be predicted, the study concept inevitably includes full-term children – mother pairs to be included. Pregnant women under the age of 18 years and women, who do not plan to deliver their infant at our site will be excluded primarily, because in these cases collecting the samples postpartum is not feasible. Women who decline to feed their infant with breast milk or without written consent will also be excluded.

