### Primary endpoint, secondary endpoints/data collection

The primary endpoint is the HMO composition (3-fucosyllactose, 3’-sialyllactose) in human breast milk after supplementation prenatally. Secondary endpoints are clinical and safety outcomes of mothers (infections, alterations in vaginal microbiome) and infants (preterm birth, sepsis, growth, gastrointestinal complications) and the effects on the microbiome composition in the rectovaginal tract of mothers at delivery and in the gut of term and preterm infants.

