### Data collection

Standardized Case Report Forms (CRFs) are used to record information from the mother prenatally and postnatally from mother and infant. At the time of inclusion (CRF inclusion), closely after birth (CRF day 3), one month after birth (CRF day 28), at three months CRF 3 m (mother + infant), one- and five-year follow- up (CRF 12 and 60 m) (see Fig. 2).

Data collected at the follow-ups will be used to measure long-term outcomes (allergies, incidence of infections, re-admissions to the hospital). The CRFs are filled in manually by the study team (neonatologist, doctoral student and study nurse). Additionally, the women will be asked to keep a diary handed out at inclusion to document regularity of probiotic intake, infections, antibiotic therapy, allergies and possible side effects during the intake of probiotics. The inclusion-CRF collects information of former participant’s medical history e.g. preexistent diseases, the course of pregnancy, former pregnancies and allergies. The follow up CRFs collect data from both, mothers and infants. CRF day 3 includes information about the delivery mode, reason for delivery, infections and risk factors for microbiome dysbiosis. In CRF day 28 information about complications in puerperium, growth parameters and feeding of the infant is collected. This data will be collected via telephone interview. In case of birth before completed 32 weeks follow-up examination will take place onsite. At follow-up information on both, mother and infant will be recorded via CRFs.

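### Two exploratory subgroup factors, indication for delivery and infections in pregnancy, are wholly or partly post-randomisation; define subgroups from data at inclusion instead

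*Protocol article*

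**What the plan says.** All references are to the protocol article.

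- **Subgroups (Statistical analysis).** "Subgroup analysis of previous medical history exposure to antibiotics, infections in pregnancy and indication for delivery will be performed on an exploratory basis".
- **Recall (same section, next sentence).** "Adjustments for recall rate (diary, survey data) will be performed, we aim for a recall-rate of > 75" percent. The variables and model concerned are not stated.
- **After birth (Data collection).** "CRF day 3 includes information about the delivery mode, reason for delivery, infections and risk factors for microbiome dysbiosis".
- **During intake (Data collection).** A diary handed out at inclusion is to "document regularity of probiotic intake, infections, antibiotic therapy, allergies and possible side effects during the intake of probiotics".
- **At inclusion (Data collection).** "The inclusion-CRF collects information of former participant’s medical history e.g. preexistent diseases, the course of pregnancy, former pregnancies and allergies".
- **Endpoints (Primary endpoint, secondary endpoints/data collection).** Secondary endpoints include "clinical and safety outcomes of mothers (infections, alterations in vaginal microbiome") and, for infants, preterm birth.
- **Entry (In- and exclusion criteria).** On who may enrol, and when: "Pregnant women of any ethnic background between 20 + 0 and 36 + 6 weeks of pregnancy who are at risk for preterm birth are included".

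Treatment is open label without placebo (Intervention/Control). Analysis details are deferred to a statistical analysis plan, to be finalised before the last patient is included.

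**The concern.** Randomisation makes the arms comparable at inclusion. A subgroup fixed at inclusion inherits that comparability. A subgroup fixed later does so only if treatment has no influence on who enters it.

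This trial cannot presume the absence of such an influence. It hypothesises a change in the vaginal flora, and it lists maternal infections and preterm birth as outcomes. If the probiotic prevented some infections, the women still infected in the two arms would differ in susceptibility. If susceptibility is also related to milk oligosaccharides, a difference between arms can appear within a stratum without any treatment effect, or a real effect can be masked.

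There is also a question of use. The article says the results may bear on the management of pregnancies at risk. An effect reported by indication for delivery cannot guide a decision made at enrolment, because the indication is not yet known. The risk condition at enrolment is known.

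**Working it through.** **1. Timing of each factor**

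| Factor | Where recorded | Relation to randomisation |
|---|---|---|
| Previous medical history | Inclusion CRF | Before |
| Antibiotic exposure | Wording can be read as history; therapy is also in the diary | Before, or mixed |
| Infections in pregnancy | Course of pregnancy on inclusion CRF; later ones in diary and on CRF day 3 | Mixed: at least 20 weeks before inclusion, plus the time to delivery |
| Indication for delivery | CRF day 3 | After, for every woman |

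Nothing in the article limits the infection factor to the period before inclusion.

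**2. Yardstick from the plan**

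The sample size rests on 3-fucosyllactose (Table 2): 413 [164] versus 312 [232].

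- Common SD = √((164² + 232²)/2) = 200.9
- Standardised difference = 101/200.9 = 0.503
- Two-sided alpha 0.05 (sidedness assumed), power 0.80: n = 2(1.960 + 0.842)²/0.503² = 62.1
- Dividing by a Mann-Whitney efficiency of 0.864 gives 71.9, so 72 per group against the stated 73

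The plan's figure reproduces to within one woman. The present point does not change it; 0.50 SD serves only as the scale for the bias.

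**3. Size of the bias, with assumed inputs**

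None of these inputs is in the documents: true oligosaccharide effect 0; infection after randomisation 30% in controls and 15% with probiotics; an unmeasured frailty correlated 0.4 or 0.6 with infection liability and 0.4 with oligosaccharide level. The correlation of liability with level is then r = 0.4 × 0.4 = 0.16 or 0.6 × 0.4 = 0.24.

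With a normal liability, threshold t, density φ(t) and infection probability p, the mean level is r·φ(t)/p in infected women and −r·φ(t)/(1 − p) in uninfected women.

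- Controls: φ(0.524) = 0.3477; 0.3477/0.30 = 1.159; −0.3477/0.70 = −0.497
- Probiotics: φ(1.036) = 0.2332; 0.2332/0.15 = 1.554; −0.2332/0.85 = −0.274

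| Spurious arm difference (SD) | r = 0.16 | r = 0.24 |
|---|---|---|
| Infected: (1.554 − 1.159)·r | 0.063 | 0.095 |
| Uninfected: (−0.274 + 0.497)·r | 0.036 | 0.053 |
| Interaction (difference of the two) | 0.028 | 0.042 |

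A simulation of 2,000,000 women agrees: 0.063 and 0.099 in infected women, 0.035 and 0.052 in uninfected women. If frailty lowers the oligosaccharide level, the signs reverse.

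**4. Comparison with sampling error at 73 per arm**

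- Infected: 73 × 0.30 = 21.9 and 73 × 0.15 = 10.95; SE = √(1/21.9 + 1/10.95) = 0.37 SD
- Uninfected: 51.1 and 62.05; SE = √(1/51.1 + 1/62.05) = 0.19 SD
- Interaction: √(0.37² + 0.19²) = 0.42 SD

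With these biases, a two-sided 5% test has a true type I error of about 5.3% to 5.9% within strata and about 5.1% for the interaction.

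**5. Sensitivity to the treatment effect on the event**

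A second simulation used an event rate of about 30%, a log-odds of 1.0 per SD of frailty on the event, and 0.3 to 1.0 SD of frailty on the outcome. The within-stratum bias was about 0 at an odds ratio of 1.0, about 0.02 to 0.06 SD at 0.7, and about 0.03 to 0.11 SD at 0.5. The whole-group comparison stayed at about 0 throughout.

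No size is computed for indication for delivery or for recall; the documents give nothing from which to set inputs.

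**The case against.** The strongest reply is that nothing confirmatory is affected. The subgroups are labelled exploratory, the primary endpoint does not use them, and the unseen analysis plan may fix their definition and timing. Moreover, the illustrative bias is far below the sampling error, and in an interaction test the two stratum biases have the same sign and largely cancel.

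Most of this stands and limits the weight of the point. It does not remove it. The article itself names the factors, so a later plan would inherit them, and indication for delivery has no baseline version under that name. The exploratory label warns about multiplicity and strength of evidence; it does not make the strata comparable.

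Two stronger readings are tempting, and the documents do not support them.

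- A reader might infer that all these subgroups are post-randomisation. Medical history is a sound baseline factor, antibiotic exposure can be read as one, and infections are partly baseline because women enter at 20 weeks or later. The fault for infections is that earlier and later ones are not separated.
- A reader might infer that the oligosaccharide results will be adjusted for diary recall. The text says "Adjustments for recall rate (diary, survey data) will be performed" and ties this to diary and survey data, whereas oligosaccharides are measured in milk by NMR. It may mean no more than a correction for survey non-response. Nor is the diary relevant only to the probiotic arm: it also covers infections, antibiotics and allergies.

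**Conclusion.** The point holds in limited form. Indication for delivery is a post-randomisation factor for every participant. Infections in pregnancy is a mixed factor that overlaps a secondary endpoint. Arm comparisons within these strata lose the protection of randomisation if the probiotic affects the events.

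The likely size is small: about 0.04 to 0.09 SD within infection strata (up to 0.11 SD in the second model) and about 0.03 to 0.04 SD on the interaction, against a standard error near 0.42 SD and a planning difference of 0.50 SD. These figures rest wholly on assumed inputs, and the bias is nil if treatment does not change the event. The primary comparison is untouched.

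The recall issue is conditional. It matters only if recall enters the oligosaccharide arm comparison, because diary completion is behaviour after randomisation in an unblinded trial.

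**What to change.** In the statistical analysis plan, which the article leaves open until before the last inclusion:

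1. Define subgroups only from data at inclusion: previous medical history; the risk condition at enrolment (PPROM, cervical shortening, bleeding, preeclampsia/HELLP); and infections and antibiotic exposure dated before randomisation.
2. Test each with a treatment-by-baseline interaction term, still labelled exploratory.
3. Report indication for delivery and infections after randomisation descriptively by arm, or as outcomes.
4. State what the recall adjustment applies to. Limit it to diary and survey variables and keep it out of the oligosaccharide arm comparison.

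The cost is wording only. The enrolment condition is known for every woman, and the inclusion CRF covers medical history and the course of pregnancy; check that it captures infections and antibiotics before inclusion with dates. The downside is that the descriptive tables will no longer give an effect estimate by delivery indication.

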## Background and literature research

Human Milk Oligosaccharides (HMOs) are the third largest component of human milk [2, 3]. Reported concentrations range from 5-15 g/l in mature milk up to 20 g/l in colostrum [2, 4]. More than 200 different HMOs have been identified although < 20 of them account for > 90% of total content [5]. HMO concentrations differ depending on maternal factors (age, parity, diet, ethnicity) [6], lactation period, length of gestation and mother’s genetic secretor status [4]. Glycosyltransferases synthesize five monosaccharides (ß-D-galactose(Gal), ß-D-glucose(Glc), ß-*N*-acetylglucosamine(Glc*N*Ac), α-L-Fucose(Fuc) and α-D-*N*-acetylneuraminic acid (Sia)) into the different HMOs [2, 5] in the Golgi apparatus of the mammary gland cells. The concentrations of HMOs in human milk vary greatly depending on the maternal expression of the secretor gene (FUT2) and the Lewis gene (FUT3) [7, 8]. Dominant (Se) and recessive (se) alleles are differentiated and mothers can be divided in ”secretors” and “non-secretors” with and without at least one dominant allele [9–11]. Hence, the total amount of HMOs in ”non-secretors” women’s milk is significantly lower compared to that of ”secretors” [12].

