### Intervention/Control

Study participants are randomly assigned to receive the probiotic mixture (intervention group *n* = 73) or not (control group *n* = 73). The intervention is one capsule of Bactiol^®^ Infantis per day until delivery. The proposed number of participants is calculated based on former studies (see below). A randomization sequence was created in advance to assign mother – infant pairs to a study arm. This trial is not blinded. The women and participating doctors know whether they are in the intervention or control group, and we are not using a placebo.

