### Sample collection

After informed consent the participants take one capsule of probiotics once daily until delivery. At the timepoint of inclusion, samples to describe the “baseline microbiome” will be collected in the form of a rectovaginal swab and a stool sample. As soon as labor begins or imminent delivery is likely, a rectovaginal swab and stool sample are taken by a midwife or obstetrician to test hypothesis 2 (increased abundance of *Lactobacillus* and *Bifidobacteria* in women’s vaginal flora due to probiotics supplementation in pregnancy). After birth samples of colostrum, breast milk and neonatal stool are gathered on day one, two, three, seven, fourteen and 28, stored and frozen at -80 °C. Depending on gestational age, stage of enteral feeding, and growth, preterm infants are fed exclusively breastmilk, donor milk, formula milk or a mixture. This will be considered in the final analysis. Additional samples (a stool sample of the infant and a breast milk sample from the mother when still breastfeeding) will be collected at the follow-up visit at three-month, 1 year and 5 years of age by study personnel. A standardized questionnaire about former parents’ history, infections, allergies, postpartum course, provided by the families in the first week, completed by case report forms at day 3, day 28 and at three months, one year and five-year follow-up (see Fig. 2).

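### The protocol plans to adjust the HMO comparison for duration of probiotic intake, which is set at delivery and has no value in controls, and to read a necessary duration from it; entered as written, the adjusted arm effect is not the randomised effect

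*Protocol article*

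**What the plan says.** Under Statistical analysis the protocol article states: "The duration of probiotic intake will be taken into account in the final analysis". The next sentence gives the method: "We will adjust our data for the different intervention timeframes using matched pair and multivariate regression analyses". If an effect on HMO concentration is observed, the article adds, "we will also determine the necessary duration of supplementation as a result of this study". Neither the adjustment nor the duration claim is labelled exploratory.

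Other sections fix what this variable is:

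- **When it ends.** Sample collection: "After informed consent the participants take one capsule of probiotics once daily until delivery".
- **Controls.** Intervention/Control: the control group receives no probiotic, and "we are not using a placebo".
- **Delivery timing is an outcome.** The secondary endpoints list "infants (preterm birth, sepsis, growth, gastrointestinal complications".
- **Gestation and the primary endpoint.** The Background names "lactation period, length of gestation" among the factors on which HMO concentrations depend.
- **Entry window.** Women enter between 20+0 and 36+6 weeks (Screening and study participants).

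No timeframe is defined for controls. Intention-to-treat appears only under Stopping rules, in connection with recording data.

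**The concern.** Adjustment protects a randomised comparison when the covariate is fixed before randomisation. Duration of intake is not. It equals gestational age at delivery minus gestational age at entry, so it is settled after randomisation by an event that treatment may influence.

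Two results are at stake. The first is the HMO comparison. If intake duration is entered beside arm, with 0 for controls, the arm coefficient becomes the estimated effect at zero days of intake, which is not what the trial was sized to detect. The second is the necessary duration. Duration is not randomised. Women with longer intake differ in gestational age at entry and at delivery, so a trend in HMO level across duration can appear without any effect of duration, and would then be reported as a trial result.

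**Working it through.** **1. The plan's own figure.** Table 2 gives 3-fucosyllactose as 413 [164] against 312 [232].

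- Pooled SD = √((164² + 232²)/2) = 200.9; difference = 101; standardised difference = 101/200.9 = 0.503.
- Two-sided alpha 0.05 (sidedness is not stated; two-sided reproduces the table), power 0.80, Mann-Whitney factor π/3: n = (π/3) × 2 × (200.9 × 2.8016/101)² = 65.04 per arm.
- With 10% dropout: 65.04/0.9 = 72.3, so 73, as stated.

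The sample size is not in dispute. It was derived for an unadjusted two-arm comparison.

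**2. What zero-coding does to precision.** Fit outcome = a + b·arm + c·D, with D = intake duration and D = 0 in controls. Then b is the fitted treated mean at D = 0 minus the control mean, and its variance is that of the unadjusted difference multiplied by

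1 + mean(D)² / (2 × SD(D)²).

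The documents do not give the spread of D, so it is assumed. With mean intervals of about 5 weeks and a range of gamma shapes, the multiplier is about 1.6 to 3.4. For 66 per arm (73 × 0.9 = 65.7) and a standardised difference of 0.5:

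| Variance multiplier | Expected z = 0.5 × √(66/2) / √multiplier | Power, normal approximation |
|---|---|---|
| 1 | 2.87 | 82% |
| 1.6 | 2.27 | 62% |
| 3.4 | 1.56 | 34% |

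Simulation gives about 82% falling to 59-33%.

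**3. What zero-coding does to the estimate.** In this model

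adjusted arm effect = unadjusted arm effect − (slope of outcome on D within the probiotic arm) × mean(D).

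A separate simulation used 73 per arm, residual SD 200.9, 3000 runs, entry uniform over 20 to 36.9 weeks and mean interval about 5 weeks. The gestation slope of ±15 units per week (15/200.9 = 0.075 SD) is assumed.

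| Scenario | Unadjusted effect | Within-arm slope × mean D | Adjusted effect (simulated) | Rejection rate, unadjusted → adjusted |
|---|---|---|---|---|
| Constant effect, no gestation link | 101 | −0.1 × 5.0 | 102 | 0.86 → 0.68 |
| Effect proportional to duration | 107.8 | 21.4 × 5.03 | 0.2 | 0.85 → 0.05 |
| Constant effect, HMO +15 per week | 101.0 | 8.3 × 5.01 | 60 | 0.80 → 0.27 |
| Constant effect, HMO −15 per week | 101.4 | −8.25 × 5.02 | 143 | 0.81 → 0.89 |

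In the first row the SE goes from 33.2 to 41.6, a variance ratio of (41.6/33.2)² ≈ 1.57, with no bias. In the other rows the estimate moves by the slope times the mean duration.

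**4. The alternative covariate.** Using the enrolment-to-delivery interval in both arms recovers the arm effect: 101 with a constant effect, 107 with a proportional one. If treatment prolongs the interval and delivery timing shares a cause with HMO level, the estimate shifts by about −4 units (97.1 against 101.1).

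**5. The necessary duration.** In the ±15 rows there is no true relation between duration and effect. Even so, the slope within the probiotic arm averaged about +8.3 or −8.3 units per week and was significant in about 34% of runs. Across assumed gestation trends of 0.05-0.10 SD per week, it was falsely significant in about 11-76% of simulated trials with no probiotic effect. An arm-by-interval interaction using the controls' own interval kept its error rate at 4-5%.

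**The case against.** The article never says that intake is coded 0 in controls. Matching across arms needs a control value, and the natural candidate is the inclusion-to-delivery interval, which does far less harm. The trial is sized on an unadjusted Mann-Whitney test, the duration question is raised only if an effect of therapy is seen, and details are left to a statistical analysis plan that is not shown. The size of the harm depends on interval lengths and a gestation trend that the documents do not give.

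Much of this stands, and it rules out three stronger readings:

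- **That the adjusted effect is necessarily biased or wiped out.** This depends on zero-coding and on either a duration-dependent effect or a gestation-HMO link. Without those two, only precision is lost.
- **That duration can never be studied here.** An arm-by-interval interaction can inform the question if treatment does not change the interval. What fails is a necessary duration read from a trend among treated women.
- **That the delivery-indication subgroup is an error of the same weight.** The article already says that analysis by "indication for delivery will be performed on an exploratory basis", so it is a minor matter.

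What does not stand is leaving it all to the analysis plan. This is not an omitted detail. The article names the covariate as intake, names the methods and promises the result. A plan that follows it inherits the problem.

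**Conclusion.** The point holds in conditional form. The protocol commits, without an exploratory label, to adjusting for a post-randomisation variable that controls do not have, and to determining a duration from it.

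If intake is entered as written with 0 in controls, variance rises about 1.6- to 3.4-fold, power falls from about 82% to 59-33%, and the arm coefficient goes to about 0 under a proportional effect. These figures rest on assumed intervals averaging about 5 weeks. With the interval defined in both arms, the arm effect is essentially intact provided treatment does not change that interval. Because preterm birth is a secondary endpoint, that condition cannot be taken for granted.

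A necessary duration taken from the treated women would be a confounded, non-randomised association. The 11-76% false-positive range rests on the assumed trend of 0.05-0.10 SD per week; the article says gestation matters but gives no size or direction.

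**What to change.** In Statistical analysis, and in the analysis plan:

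1. State that the primary HMO comparison is between the randomised arms, with no adjustment for or matching on intake duration, and with adjustment only for baseline covariates such as gestational age at randomisation.
2. Examine duration separately, through an exploratory arm-by-interval interaction using the randomisation-to-delivery interval in both arms. Note that this assumes treatment does not change the interval.
3. Replace the promise to determine a necessary duration with a statement that the association with duration will be explored.

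The cost is wording only. No new data are needed and 73 per arm is unaffected. The duration claim becomes exploratory.
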